## Abstract

**Background:**

Elevated cholesterol levels and systemic inflammation are considered relevant risk factors for cardiovascular disease (CVD) development and progression. Increasing evidence suggests that cholesterol-lowering and inflammation-lowering nutraceuticals are useful in the management of moderate hypercholesterolemia. Here, we describe the study protocol of a clinical trial aimed to evaluate the cholesterol and inflammatory lowering effect of an innovative dietary supplement (BruMeChol™, Mivell S.r.l., Italy), composed of a mixture of extracts of bergamot and olive fruits in association with vitamin K2 in subjects with mild hypercholesterolemia.

**Methods:**

The study was planned as a randomized, double-blind, placebo-controlled, parallel group clinical trial for 12 weeks at the Cardiology Unit of the IRCCS INRCA of Ancona, Italy. A total of 125 subjects (age ≥ 40 years) with mild hypercholesterolemia (total serum cholesterol levels ≥ 200 and ≤ 250 mg/dl) will be recruited. Intervention arm participants will take one capsule of dietary supplement two times a day, 15 min before the main meal. Control arm participants will receive one capsule of placebo in the same way. The dietary supplement capsule contains the following ingredients: phytosterols, flavonoid-rich extract of bergamot fruit (*Citrus bergamia*), flavonoid-rich extract of olive fruit (*Olea europaea*), and vitamin K2. Participants will undergo a medical evaluation and chemical-clinical examinations, which include lipid profile, glycemia, biomarkers of renal, liver and cardiac/muscular functions, interleukins (IL 6, IL-32, IL-37, and IL-38), and innovative mediators of inflammation such as inflamma-miRs (miR-21 and miR-146a), at baseline, and after 6 and 12 weeks of treatment. The decrease in total cholesterol levels and inflammatory biomarkers will be the primary and secondary endpoints of the study.

**Discussion:**

This protocol study, planned to verify the effects of BruMeChol™ dietary supplementation in subjects with mild hypercholesterolemia, could also contribute to new study designs for next large-scale multicenter clinical trials.

**Trial registration:**

Australian New Zealand Clinical Trials Registry: ACTRN12619000170123. Retrospectively registered on 5 February 2019

## Background

Cardiovascular diseases (CVDs) in industrialized countries are the leading cause of morbidity and mortality and one of the most widespread diseases with expensive health care [1, 2]. Elevated serum cholesterol concentrations (hypercholesterolemia) are one of the main risk factors for atherosclerosis progression that can lead to myocardial infarction, stroke, and peripheral vascular disease.

Statins are the reference drug for the treatment of hypercholesterolemia. However, patients with indications for the statin therapy as primary prevention most often prefer not to take the drugs for possible side effects and attempt to reduce the total cholesterol levels in serum by improving their lifestyle. The lifestyle changes recommended are smoking cessation, no alcohol consumption, increasing physical activity, and maintaining a healthy weight [3]. When all these efforts do not give results, the intake of nutraceutical substances could be considered in improving the lipid profile.

Increasing evidence supports the beneficial effects of plant components and vitamins in maintaining the physiological levels of serum cholesterol, thus contributing to the prevention of atherosclerosis. Plant polyphenols are the starting point in developing new supplements designed to improve chronic inflammatory states, combat atherosclerosis, and the risk of thrombosis related to CVDs [4]. *Citrus bergamia*, also known as bergamot, has shown a significant degree of hypocholesterolemic as well as antioxidant/radical effects [5]. In particular, this fruit has flavanones that can act as natural statins [6]. The use of natural bergamot-derived polyphenols may allow patients undergoing statin treatment to reduce effective doses [7]. Olive tree polyphenols have properties of medical interest like anti-atherogenic, antihepatotoxic, hypoglycemic, anti-inflammatory, antitumor, antiviral, and immunomodulatory activities [8, 9]. Phytosterols are constituents of plant cell walls. Due to the structural similarity with cholesterol, when they are ingested with plant foods, they reduce cholesterol absorption from the gut. It was shown that the intake of plant sterols of 1.6–2 g a day reduces cholesterol absorption from the gut of 30%, as well as plasma low-density lipoprotein (LDL) cholesterol levels of 8–10% [10]. The role of vitamin K2 in atherosclerosis prevention is based on its ability to activate a group of proteins that keep calcium in the bones, out of the arteries [11–13]. When there is a lack of vitamin K2, these proteins cannot be activated, resulting in calcium loss [14, 15].

Starting from the knowledge of the beneficial effects of each abovementioned compound on cholesterol levels, we hypothesized that a new dietary supplement consisting of a mixture of flavonoids extracted from bergamot, olive polyphenols, plant sterols, and vitamin K2 could reduce total cholesterol levels also through their synergistic effect. Besides, it could also prevent atherosclerotic plaque formation by its antioxidant and anti-inflammatory properties.

## Methods/design

### Hypothesis

We hypothesized that the intake of this new dietary supplement, containing molecules with potential effects on lipid metabolism, could reduce after 12 weeks the total cholesterol levels in serum of subjects with mild hypercholesterolemia. We also hypothesize that this dietary supplement could decrease serum level of circulating inflammatory marker such as high-sensitive C-reactive protein (*hs*-CRP), as well as particular interleukins and specific circulating inflamma-miRs.

### Primary objective

The primary aim of the study is to evaluate the efficacy and safety of BruMeChol™ dietary supplement to reduce total cholesterol levels in serum of patients with mild hypercholesterolemia.

### Secondary objectives

The study will evaluate the change in levels of circulating inflammatory marker like hs-CRP and inflammatory cytokines such as interleukin 6 (IL6) [16], interleukin 32 (IL32) [17], interleukin 37 (IL37) [18], and interleukin 38 (IL38) [19], as well as a variation in the expression of specific circulating inflamma-miRs (miR-21 and miR-146a) [20]. Moreover, the association between cardiovascular (CV) risk score and lipidic and inflammatory parameters measured at baseline will be evaluated.

### Study design

This interventional, randomized, double-blind, placebo-controlled clinical trial for 12 weeks will evaluate the effect of the new dietary supplement in reducing total serum cholesterol levels. The study will be conducted at the Cardiology Unit of the IRCCS INRCA of Ancona, Italy. The subjects’ involvement in the study will end after 12 weeks. The study has been retrospectively registered with the Australian New Zealand Clinical Trials Registry (ACTRN12619000170123). Figure 1 provides an overview of the study.

**Fig. 1 Fig1:**
[figure not shown]
Schematic representation of study design

### Sample size and statistical considerations

In the present study, 125 subjects will be recruited, randomized according to a 1:1 ratio in the intervention and the control arm. To find a significant difference in cholesterol levels between the two treatments (BruMeChol™ vs. placebo) at the end of the 2nd follow-up, assuming a medium effect size of the proposed treatment (*d* = 0.5), we should study at least 118 subjects (at least 59 for treatment arm) with a power of 0.85 and a type I error probability of 0.05. By providing a dropout rate of 5%, a total of 125 participants must be recruited.

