### Statistical analysis

Demographic, clinical characteristics and outcomes data will be summarized with counts and percentages for categorical variables, means (standard deviations) for normally distributed continuous variables, and medians (with interquartile ranges) for other continuous variables. Kolmogorov-Smirnov test will be used to check the normality of the related variables. Repeated measures analysis of variance (ANOVA) will be used to test whether treatment (between-subjects factor) differentially affect the mean values of cholesterol levels (within-subjects factor) over time. The same analysis will be also repeated for the inflammatory biomarkers that will be used as within-subjects’ factors. Mauchly’s test will be used to assess the assumption of sphericity, and Greenhouse-Geisser correction will be adopted for violations of this assumption. A significant level of 0.05 will be used throughout the study. Statistical analyses will be performed with IBM SPSS statistical software ver. 25.0 (IBM Corp., Armonk, NY, USA).

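### The 118 subjects for 85% power match a one-sided t-test that the protocol never declares; a two-sided 0.05 comparison of 12-week means has about 77% power

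*Protocol article*

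**What the plan says.** The section on sample size and statistical considerations describes a 1:1 comparison of supplement and placebo at the end of the second follow-up (12 weeks), with a medium effect of d = 0.5. The stated aim is "To find a significant difference in cholesterol levels between the two treatments", and the result is "at least 118 subjects (at least 59 for treatment arm) with a power of 0.85 and a type I error probability of 0.05". Allowing 5% dropout, 125 are to be recruited. The section names no test, no sidedness and no correlation between visits.

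The Statistical analysis section says: "Repeated measures analysis of variance (ANOVA) will be used to test whether treatment (between-subjects factor) differentially affect the mean values of cholesterol levels" over time, and "A significant level of 0.05 will be used throughout the study". The Hypothesis section expects that the supplement "could reduce after 12 weeks the total cholesterol levels in serum of subjects with mild hypercholesterolemia". That is an expected direction of effect. It is not a rule that the test will be one-sided.

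**The concern.** A type I error of 0.05 quoted without sidedness is ordinarily read as two-sided, and the planned ANOVA F-test rejects for a difference in either direction. If the sample size was derived for a one-sided test, the stated 85% does not describe a two-sided comparison with the same 118 subjects.

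What is at stake is the power claim for the primary endpoint. If the true effect is d = 0.5, a two-sided comparison of 12-week means misses it about 23% of the time, against the 15% that the protocol implies. Anyone weighing a null result needs the right figure. The mismatch does not bias the treatment estimate or inflate the type I error.

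**Working it through.** **Inputs** (all from the sample-size section): d = 0.5; 59 per arm; alpha 0.05; power 0.85; 1:1 allocation; dropout 5%.

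**Formula.** For a two-sample t-test with n per arm, the noncentrality is δ = d·√(n/2), with 2n − 2 degrees of freedom. Power is the probability that a noncentral t with that δ exceeds the critical value.

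**Step 1: reproduce the plan's figure.** At n = 59, δ = 0.5 × √29.5 = 2.716 with 116 degrees of freedom.
- One-sided 0.05 (critical value 1.658): power 0.854. At 58 per arm it is 0.849, so 59 is the smallest size reaching 0.85, and 2 × 59 = 118.
- Dropout: 118 / 0.95 = 124.2, rounded up to 125. This also reproduces.

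**Step 2: the same inputs, two-sided** (critical value 1.981 at 59 per arm).

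| Evaluable | Two-sided 0.05 power at d = 0.5 |
|---|---|
| 118 (59 per arm) | 0.768 |
| 125 (average 62.5 per arm) | 0.792 |
| 144 (72 per arm) | 0.846 |
| 146 (73 per arm) | 0.851 |

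A two-sided 85% therefore needs 146 evaluable, or 146 / 0.95 = 153.7, rounded up to 154 recruited. With 59 per arm, the effect detectable with 85% two-sided power is d = 0.556.

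**Step 3: the planned analysis.** The 0.768 belongs to a t-test of 12-week means, not to the repeated measures ANOVA. For the treatment-by-time F-test over three visits, I assume compound symmetry with correlation ρ. The noncentrality is λ = (n/2) × Σ(Δ_j − mean Δ)² / (1 − ρ), with 2 and 232 degrees of freedom, where Δ_j is the arm difference in SD units at visit j. Take n = 59:
- Differences 0, 0.25, 0.5 at baseline, week 6 and week 12: the sum of squares is 0.125.
- Differences 0, 0.5, 0.5: the sum of squares is 0.167.

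| Assumed ρ | Half effect at week 6 | Full effect at week 6 |
|---|---|---|
| 0.3 | 0.52 | 0.65 |
| 0.5 | 0.67 | 0.80 |
| 0.6 | 0.78 | 0.89 |
| 0.7 | 0.89 | 0.96 |

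Both ρ and the week-6 effect are my assumptions; the protocol gives neither.

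**Step 4: baseline-adjusted ANCOVA at 12 weeks.** Adjustment shrinks the residual SD by √(1 − r²), where r is the baseline to 12-week correlation, so the effective d is 0.5/√(1 − r²). Two-sided power at 59 per arm:
- r = 0.3: effective d = 0.524, power 0.806
- r = 0.44: effective d = 0.557, power 0.851
- r = 0.5: effective d = 0.577, power 0.875

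These values of r are also assumptions.

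**The case against.** **118 can be reached two-sided.** A repeated-measures calculation for the between-subjects effect (f = 0.25) gives power 0.853 with 118 subjects, either from three measurements at correlation 0.7 or from two at 0.6. This stands: it would be wrong to say that the stated figure can arise only from a one-sided test. Those routes need a correlation that the protocol does not state, and they test an effect averaged over visits. The section describes a single contrast at the second follow-up, which a one-sided t-test matches exactly on the stated inputs alone. How the figure was obtained remains an inference.

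**The planned test does not have 77% power.** A reader might infer that it does, or that the trial as planned misses a true d = 0.5 effect 23% of the time. The document does not support either. Those figures belong to a comparison of 12-week means, and Step 3 shows that the planned ANOVA could lie well below or well above them.

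**The hypothesis is directional, so a one-sided calculation may have been intended.** That could explain the number. It does not reconcile it with a non-directional F-test at 0.05.

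**Baseline adjustment would recover the power.** It would if the correlation is at least about 0.44. The protocol offers no figure for it, and entry is restricted to total cholesterol of 200 to 250 mg/dL, which tends to lower the correlation of baseline with follow-up. This route is therefore conditional.

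**Conclusion.** The concern holds in limited form. On the stated inputs, 85% power with 118 subjects is correct for a one-sided 0.05 t-test, which the protocol never declares. For a two-sided 0.05 comparison of 12-week means the power is about 77%, roughly 8 points lower, and it stays at 79% even with no dropout. This rests on exact t calculations with equal arms and on d = 0.5 being the standardised between-arm difference at 12 weeks. The power of the planned repeated measures ANOVA is undetermined: it ran from 0.52 to 0.96 over the assumed correlations and week-6 effects. The stated power therefore cannot be relied on as written, but the document does not show that the planned analysis is underpowered by any particular amount.

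**What to change.** Restate the sample-size section as two-sided: with 118 evaluable subjects, a 0.05 comparison of 12-week means has about 77% power for d = 0.5, or 85% power for d = 0.56. No further enrolment is needed. The cost is one paragraph and a less favourable power figure.

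Alternatively, make the primary test in the Statistical analysis section a two-sided ANCOVA of 12-week total cholesterol adjusted for baseline, and base the power on it. State the assumed correlation openly as an assumption: 0.3 gives 81%, 0.44 gives 85% and 0.5 gives 87%. This changes the primary analysis as well as the wording, so it should be settled before unblinding, and the power then depends on a correlation that must be justified. Either way, the test that is powered should be the primary test that is run.

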### Population

Subjects of 40 years or over afferent to the outpatient facilities of the Cardiology Unit for a medical check will be invited by the research staff to participate in the study. Subjects who meet the inclusion criteria and wish to participate in the trial procedure will have to sign a written informed consent. A total of 125 voluntary subjects with mild hypercholesterolemia will be enrolled. Trial staff will have the responsibility to withdraw enrolled patients at any time if they fail to meet the inclusion criteria.

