### Inclusion criteria

Both genders, age of 40 years or over.Total blood cholesterol levels ≥ 200 and ≤ 250 mg/dL.No history of clinically relevant cardiovascular events.

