### Randomization

After checking the inclusion and exclusion criteria, subjects’ randomization into the two parallel treatment arms will be carried out by the distribution of a blinded treatment kit containing test or placebo capsules. The capsules will be randomly assigned into the test and placebo groups at a 1:1 ratio according to the random number generated by SPSS v25.0 software package (SPSS Inc., Chicago, IL, USA).

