### Outcomes

#### Primary outcome

The primary outcome is the change in serum total cholesterol levels after 12 weeks of post-intervention commencement between experimental arm and placebo comparator arm.

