##### Biochemical profile

Screening visit will include following measurements: total cholesterol, fasting glucose, liver profile (AST/GOT, ALT/GPT), kidney profile (creatinine, CKD-EPI e-GFR) and thyrotropin (TSH). Serum lipid profile: total, LDL, HDL cholesterol and triglycerides, liver profile (AST/GOT, ALT/GPT), kidney profile (creatinine, CKD-EPI e-GFR), fasting glucose, fool blood exam (FBE), leukocyte formula, electrolytes, cardiac/muscular markers (CK/myoglobin), CRP, and Lp(a) will be measured at baseline, 6 weeks, and on completion of the study (12 weeks from randomization). All items that will be measured at every visit are described in Table 2.

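### The withdrawal sentence has no time limit and the cholesterol criterion is tied to no visit, so withdrawal could depend on the primary outcome

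*Protocol article*

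**What the plan says.** All references are to the protocol article.

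- **Population:** "Trial staff will have the responsibility to withdraw enrolled patients at any time if they fail to meet the inclusion criteria". The sentence covers people already enrolled and sets no end point.
- **Inclusion criteria:** "Total blood cholesterol levels ≥ 200 and ≤ 250 mg/dL". No visit is named at which this is judged.
- **Primary outcome:** "The primary outcome is the change in serum total cholesterol levels after 12 weeks", compared between the arms.
- **Study period (Table 2) and Biochemical profile:** total cholesterol is measured at screening and again at baseline, week 6 and week 12.
- **Randomization:** kits are distributed "After checking the inclusion and exclusion criteria", which places the eligibility check before allocation.
- **Sample size and statistical considerations:** at least 118 subjects (59 per arm), "assuming a medium effect size of the proposed treatment" (d = 0.5), "with a power of 0.85 and a type I error probability of 0.05". The total is raised to 125 for 5% dropout.
- **Retention:** the reason for withdrawal is recorded. The article does not say whether a withdrawn subject's week 12 cholesterol is still collected.

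**The concern.** Three statements interact badly. Staff are given a standing duty to withdraw people who fail the inclusion criteria. One criterion is a window on total cholesterol with no date attached. Total cholesterol is also what the supplement is meant to lower and what the trial measures as its primary outcome. Of the inclusion criteria, this is the only one that the intervention is meant to move.

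A subject at 195 mg/dL at week 6 does not satisfy the criterion as printed. If staff acted on that, withdrawal would depend on the outcome. If the supplement works, more active than placebo subjects would fall below 200. The arms would then lose different numbers and different kinds of people, and the final comparison would no longer be between the groups as randomised.

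The milder meaning, withdrawing people found late to have been ineligible at entry, does not fully remove the problem. It still allows removal after allocation. The repeat lipid measurement at the randomisation visit also gives a second value on which the window could be judged, and the article does not say which value counts.

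**Working it through.** **1. The plan's own figure.** For two means, n per arm = 2(z_alpha + z_beta)²/d², with d = 0.5 and power 0.85.

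- One-sided 0.05: 2(1.645 + 1.036)²/0.25 = 57.5, so 58. The t-test version gives 58.2, so 59 per arm and 118 in total. Then 118/0.95 = 124.2, so 125. Both stated figures reproduce.
- Two-sided 0.05: 2(1.960 + 1.036)²/0.25 = 71.8, so 72. The t-test version gives 72.8, so 73 per arm. This does not reproduce 59.
- Power at 59 per arm is therefore 0.85 one-sided and 0.77 two-sided. The article does not state sidedness, so both are carried below.
- The recruitment margin is 125 - 118 = 7 subjects.

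**2. Model of the literal rule.** The article gives no SD and no effect in mg/dL, so every input here is an assumption.

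- Usual level T: mean 220, SD 30. Each reading adds independent within-person error, SD 12.
- Entry: screening reading between 200 and 250.
- Baseline = T + e1. Week 6 = T + D + e2. Week 12 = T + D + e3. D is 0 on placebo and averages -10 mg/dL on active.
- Anyone outside 200 to 250 at week 6 is removed.

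**3. Losses.**

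| Week 6 reading | Active | Placebo |
|---|---|---|
| Below 200 | 25.7% | 12.5% |
| Above 250 | 3.5% | 9.7% |
| Total removed | 29.2% | 22.2% |

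With within-person SD 15 the totals are 33.7% and 28.0%.

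A second set of assumptions used mean 225, total SD 15 to 25, within-person correlation 0.6 or 0.8, an effect of 0.5 SD, and removal only below 200 at week 6. It gave 9% to 28% lost on active and 3% to 12% on placebo. Active loss exceeded placebo loss in every scenario tried, and always exceeded 5%.

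**4. Effect on the estimate.** The primary outcome is change, and week 12 minus baseline equals D + e3 - e1. Removal at week 6 depends on T, D and e2.

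- If D is the same for everyone, removal carries no information about the change. The difference between arms stays at -10.0 mg/dL.
- If D varies between people (SD 8 to 12), those who respond most are removed most often. The difference shrinks to about -9 to -8 mg/dL.
- If a week 12 value below 200 also excluded a subject, the estimate would shrink even with a uniform response. Under the second set of assumptions the loss runs from about 4% (-7.21 against -7.47) to 16% (-10.44 against -12.48).

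**5. Effect on power.** Average loss is (29.2 + 22.2)/2 = 25.7%. From 62.5 per arm this leaves 62.5 × 0.743 = 46.4, so 46 to 47 per arm. With d held at 0.5, power at 47 per arm is:

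| | 59 per arm | 47 per arm |
|---|---|---|
| One-sided | 0.85 | 0.78 |
| Two-sided | 0.77 | 0.67 |

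**6. The milder reading.** In this model a baseline reading has the same distribution as a placebo week 6 reading. About 22% of people who passed screening would therefore read outside the window at the randomisation visit through within-person variation alone. The article does not say how such a subject is treated.

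**The case against.** The strongest reply is that nobody intended this. The sentence sits in a paragraph on invitation, consent and enrolment. The Randomization section puts the eligibility check before allocation. A trial that hypothesises a cholesterol reduction, schedules measurements to week 12 and allows 5% dropout cannot mean to remove its responders. Consent is taken at screening, so enrolled may even include people not yet randomised. This largely stands. Late-found ineligibility is the more plausible meaning.

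A reader might therefore be tempted by stronger conclusions that the article does not support:

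- *That responders will be withdrawn.* No section says that a subject whose cholesterol falls on treatment is to leave.
- *That withdrawn subjects are dropped from the analysis.* The article does not say so. Analysis sets and follow-up after withdrawal may be settled in the full protocol or the statistical analysis plan, and their absence here is no fault.
- *That the effect is necessarily attenuated.* In the model of step 2 the difference in week 12 levels falls from -10.0 to -5.9 mg/dL, but the outcome is change, and that is unbiased under a uniform response.
- *That power falls from 0.85 to 0.67.* That compares a one-sided figure with a two-sided one. Part of the gap is sidedness, a separate matter.

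What the reply does not answer is the wording itself. The Randomization section fixes when eligibility is first checked. It does not limit a sentence about people already enrolled, and nothing in the article tells staff that only the entry value counts. This is a rule the article states loosely, not a detail it leaves out.

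**Conclusion.** The point holds as a defect of wording with a real possible consequence. The sentence can be read as allowing withdrawal because of the primary outcome. On its more plausible reading it can still remove subjects after randomisation.

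The losses of 29% and 22%, the shrinkage to about -9 to -8 mg/dL, and the fall in power (0.85 to 0.78 one-sided, 0.77 to 0.67 two-sided) describe the literal rule only. They rest on an assumed mean, SDs, effect and timing of removal. The estimate moves only if response varies or if week 12 values also exclude people. The power figures assume that removed subjects do not contribute to the analysis. The direction, more loss below 200 on active if the supplement works, does not depend on the chosen SD.

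Should-fix, moderate confidence: the words are clear, the intent probably benign, and how staff apply the sentence unknown.

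**What to change.** Reword the Population sentence and the cholesterol criterion together:

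1. Limit withdrawal for failing the inclusion criteria to the time before randomisation.
2. State that the cholesterol criterion is judged once, on a named pre-randomisation value, and is not reapplied to later readings.
3. After randomisation, record late-found breaches and out-of-range values as protocol deviations, keep the scheduled visits through week 12, and analyse all randomised subjects in their allocated arm.

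Whether a subject stops taking capsules remains a separate clinical decision and need not end follow-up.

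The cost is a short wording amendment, which the Ethical approval section already says would be communicated to the ethics committee. It needs no extra visits or subjects. The article describes recruitment as still open, so the change should reach site staff promptly, because week 12 values not collected cannot be recovered.
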